### Data collection and data management

All the evaluations will be conducted by experienced psychologists. After the data are collected, all the data in the paper files will be transcribed to the Electronic Data Capture system (e Clinical Base; Translational Research Center for Medical Innovation, Kobe, Japan), which is a secure system designed for storage of personal and patient data. The data will be sent to independent data managers to assess whether the data were collected properly, focusing on the status of consent acquisition, eligibility of the participants, evaluation items, and confirmation of drop-out/terminated cases. These data managers will also oversee and review the progress of the trial. If a participant withdraws their consent, they will be dismissed from the study. At the same time, we will record the dropout rate, and the number of participants with adverse events requiring treatment. The Efficacy and Safety Assessment Committee, whose members are independent of the research, will check and assess whether the trial is conducted safely and properly, and will also decide whether to stop the trial if any severe adverse events or protocol violations occur. In addition, an on-site data monitor will conduct monitoring to ensure that the trial is performed properly, data are properly recorded, and data reliability is ensured. Audits will be also conducted independent of the researcher and sponsor. If we conduct any necessary protocol modifications, we will report them to the Clinical Research Review Board, and to the registration site of the Japan Registry of Clinical Trials website. The results of this study will be anonymized and published in relevant academic conferences and journals.

### Statistical analysis

The efficacy and safety analysis will be performed in the full analysis set, which includes all the patients who have undergone the study treatment, including those who have discontinued treatment. Missing values will not be imputed. All the reported *p*-values will be two-sided, and values of *p* < 0.05 are considered statistically significant. Data analyses will be performed using SAS (version 9.4 or later) or R (version 3.6 or later).

Baseline characteristics will be summarized using descriptive statistics according to the enrolled group. Those will be compared using chi-square tests for categorical variables and t-tests for continuous variables between groups.

#### Primary outcome

The relapse/recurrence rate will be calculated as the proportion of the patients who experienced relapse/recurrence during 12 months in each group. The odds ratio and 95% confidence interval (95%CI) will be estimated using a multivariable logistic regression model. The following covariates will be used as explanatory variables: age, sex, number of depressive episodes, duration of current depressive episode, concomitant medication, and status at enrollment (response/remission), and others to be determined prior to data fixation.

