## Materials and methods

### Study overview

This study is a multisite, prospective, non-randomized longitudinal trial, recruiting 300 participants, who will be divided into two groups: (I) the maintenance rTMS plus pharmacotherapy group and (II) the pharmacotherapy-only group. The overview of the study is shown in Fig. 1. Only patients who achieve a therapeutic response to acute rTMS therapy will be included in the study. In the maintenance rTMS plus pharmacotherapy group, patients will receive weekly treatments for 6 months, followed by bi-weekly treatments for an additional 6 months, totaling 12 months of maintenance rTMS therapy (maximum 40 sessions). During the maintenance period, the patient will continue with a stable dose of pharmacotherapy. In the pharmacotherapy-only group, patients will receive no intervention other than a continuation of concomitant pharmacotherapy and receive an evaluation. Assessments will be made at 3, 6, 9, and 12 months after the start of maintenance therapy and at the end of study participation. Random allocation to both the groups will not be performed and the patients will be classified to a group (I) or (II) according to their preferences. Owing to the long duration of maintenance therapy immediately following acute treatment in this study, conducting a double-blind, randomized, sham-controlled, parallel-group study was deemed challenging in terms of subject participation and blinding validity.

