#### Secondary and other outcomes

As for the primary outcome, the rates and between-group differences, and adjusted odds ratio (95% CI) will be estimated for the relapse/relapse rate, response rate, and remission rate at 3, 6, and 9 months after enrollment, respectively. Kaplan–Meier curves will be constructed for the duration of the sustained treatment response and sustained remission, and the log-rank test and Cox proportional hazards models will be performed for the between-group comparisons.

The change in the total scores of the HAMD-17, MADRS, QIDS, and PHQ-9 from the baseline (before the introduction of maintenance therapy) will be analyzed using a random-effects model with group, baseline total score, age, sex, time point, and interaction between the time point and the group as explanatory variables and individual as random effect, for all the data at 3, 6, 9, and 12 months.

Frequency distributions of the worst severity of the adverse events and equipment failure will be summarized. Treatment-related adverse events, serious adverse events, and discontinuations owing to adverse events will also be summarized.

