### Sensitivity analysis

As a sensitivity analysis, we will analyze the primary outcome with inverse probability of treatment weighting (IPTW) to ensure the comparability between the maintenance rTMS plus pharmacotherapy and the pharmacotherapy-only groups. The propensity score will be calculated using the covariates listed above (primary outcome section). After weighting, the covariate balance between the groups will be assessed using absolute standardized difference. Moreover, we would perform inverse probability of censoring weighted method to consider the bias attributed to the informative missing and dropout data.

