Considering feasibility and blinded validity, conducting this study as a double-blind randomized controlled trial is challenging. The total number of sessions in this study is 40 and the duration of maintenance therapy is 12 months, which is considered to be a significant burden for the participants assigned to sham stimulation owing to a large number of sessions and the long duration of the study. Moreover, since all the participants in this study received acute rTMS therapy before entering the maintenance rTMS therapy period, patients may be able to distinguish between real and sham stimulation, which would reduce the blinded validity of the study. Thus, an open-label, nonrandomized study design will be employed in this study.

As mentioned before, the risk of bias owing to the lack of blinding and randomization is a limitation of this study. For example, patients who are favorable to rTMS therapy may be more likely to be assigned to the maintenance rTMS group, resulting in a larger placebo effect and overestimating the effect of maintenance rTMS therapy. We plan to address this point in two ways. The first is to adjust for the background factors by performing IPTW analysis as a sensitivity analysis and attempting to increase the two groups' comparability. However, risk of bias remains because unmeasured confounding cannot be eliminated by an IPTW analysis. Second, the long-term outcome of post-marketing surveillance of the Nerurostar TMS device in Japan will be used as a historical control. Comparing the maintenance therapy group with both the control group in this study and the historical control group may reduce the possibility of overestimating the effect of treatment.

If maintenance rTMS is shown to be effective in preventing relapse/recurrence of depression in this study, the treatment options for patients who have had difficulty maintaining remission with antidepressants and/or psychotherapy will be expanded. Since rTMS is a developing technology, there is no evidence that the current stimulation protocol is the best for treating patients with MDD. The search for optimal protocols for rTMS maintenance therapy and updates to accommodate new rTMS stimulation methods, which are being improved daily, should be continued in future studies.

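### The primary model and the propensity score carry entry severity only as response versus remission, although the endpoint is a HAMD-17 cut-off and the month-0 score is collected

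*Protocol article*

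**What the plan says.** All references are to the protocol article.

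- **Primary outcome (Statistical analysis).** The odds ratio comes from a multivariable logistic model. Its named covariates are age, sex, how many episodes there have been, how long the current one has lasted and medication; the list ends with "status at enrollment (response/remission), and others to be determined prior to data fixation".
- **Sensitivity analysis.** "The propensity score will be calculated using the covariates listed above (primary outcome section"). Balance after weighting is then judged by absolute standardised differences.
- **Secondary and other outcomes.** The models for change in HAMD-17, MADRS, QIDS and PHQ-9 are fitted "with group, baseline total score, age, sex, time point" and a time-by-group interaction. Here the baseline score enters as a continuous covariate.
- **Covariates and outcomes.** Response is a fall of at least 50% in HAMD-17 from before acute rTMS. Remission is a total of 7 or less, and relapse/recurrence is a total of 14 or more. Table 1 schedules HAMD-17 at month 0.
- **Study overview.** "Random allocation to both the groups will not be performed and the patients will be classified to a group (I) or (II) according to their" own choice.

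**The concern.** The endpoint is the crossing of a fixed point on the HAMD-17 scale. How far a patient stands from that point at entry is therefore very likely to predict relapse. The plan measures that distance but reduces it to two classes for the primary comparison. A patient entering at 8 and one entering at 13 count as the same, although the first is six points from the endpoint and the second is one.

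If the two groups differ in entry score within a class, part of that difference passes into the primary odds ratio. The IPTW analysis is meant to make the groups comparable, but it is built on the same list and inherits the gap. A balance check limited to the listed covariates could look satisfactory while the scores themselves still differ. Agreement between the primary and sensitivity results would then say nothing about this source of bias. The secondary score models are, on this one point, better adjusted than the primary analysis, and the article gives no reason for that.

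**Working it through.** **1. How wide the classes are.** Remission covers scores 0 to 7. A responder who has not remitted has a score of 8 or more. Response is a relative criterion without a ceiling, so this class has no fixed upper end: a pre-acute score of 28 halves to 14. Within both classes the score can vary while the covariate stays constant.

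**2. The planned effect as an odds ratio.** The article gives no figure for confounding, but the sample size section gives a yardstick: a control relapse rate of 45–60% and a 20-point effect.

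- 45% to 25%: (0.25/0.75) / (0.45/0.55) = 0.41
- 60% to 40%: (0.40/0.60) / (0.60/0.40) = 0.44

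**3. Simulation with no true effect.** None of these inputs is in the document; all are assumptions. Month-0 HAMD-17 has mean about 7 and SD 3.5 (truncated at 13) or 4.5 (truncated at 18). Overall relapse is 52.5%. Log-odds of relapse rise by 0.1 to 0.3 per point. Log-odds of choosing rTMS shift by 0.06 or 0.15 per point. There are about 300,000 patients per scenario, so sampling error is small. Selected rows:

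| Truncation | Slope | Choice shift | Std. difference | Crude OR | OR, response/remission | OR, continuous score | IPTW bias on response/remission (points) |
|---|---|---|---|---|---|---|---|
| 13 | 0.1 | −0.06 | −0.19 | 0.95 | 0.99 | 1.01 | −0.3 |
| 13 | 0.2 | −0.15 | −0.45 | 0.77 | 0.91 | 1.00 | −2.1 |
| 18 | 0.3 | −0.15 | −0.55 | 0.59 | 0.83 | 1.00 | −3.8 |
| 13 | 0.1 | +0.15 | +0.45 | 1.15 | 1.06 | 1.01 | +1.3 |
| 18 | 0.3 | +0.15 | +0.55 | 1.72 | 1.22 | 1.01 | +4.1 |

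A negative shift means that lower-scoring patients choose rTMS. The positive direction was run only at the stronger shift, so 1.06 is not a floor.

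**4. Larger imbalances.** A second simulation used entry scores 0 to 13, slopes 0.15 to 0.35 and an rTMS group that enters lower. With a difference of 1.5 points, response/remission adjustment leaves an OR of 0.94 to 0.84. With 2.3 points it leaves 0.89 to 0.76. The most extreme case (2.3 points, slope 0.35) gives 0.50 crude, 0.76 with the two classes and 0.99 with the continuous score. A further run with differences of 1.3 to 2.8 points left 1.6 to 5.5 points of spurious benefit after IPTW on the two classes.

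**5. How much the two classes already remove (log OR scale).**

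- 0.59 to 0.83: 1 − ln(0.833)/ln(0.590) = 1 − 0.183/0.528 = 65%
- 0.95 to 0.99: 1 − ln(0.988)/ln(0.951) = 1 − 0.012/0.050 = 76%
- 0.50 to 0.76: 1 − 0.274/0.693 = 60%

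**6. With a true OR of 0.40** (truncation 18, slope 0.2, shift 0.15 either way): response/remission adjustment gives 0.36 or 0.48, and the continuous score gives 0.40. The IPTW risk difference is −22.5 or −16.5 points on the two classes and −19.4 on the score.

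**7. Against sampling error.** With 130 evaluable per group at 60% versus 40%, SE(log OR) = √(1/78 + 1/52 + 1/52 + 1/78) = 0.25. A residual OR of 0.89 (1.5 points, slope 0.25) is |ln 0.89| / 0.25 = 0.5 SE. A residual OR of 0.76 is 1.1 SE.

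**The case against.** **Entry score is not shown to drive group choice.** A confounder must relate to choice as well as to outcome. Nothing in the article links month-0 score to preference, and the Discussion's own example of bias is a favourable attitude to rTMS. This stands. A reader might infer that entry severity is the dominant confounder; the document does not support that.

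**The bias need not favour rTMS.** Patients with more residual symptoms may prefer to continue rTMS, and the residual bias then reverses. This also stands. A 2.3-point imbalance is about 0.5 to 0.66 SD at the assumed SDs (2.3/4.5 and 2.3/3.5), so the 0.76 end of the range is an extreme case.

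**The list is open.** The clause on further covariates would let the score, or site, be added, and the analysis plan is not shown. A reader might infer that the score is definitively excluded, or that the clause signals data-driven model choice. Neither follows: completing a covariate list before data lock is ordinary. The same holds for site and for the time point at which concomitant medication is taken. What the clause does not answer is that entry severity has already been given a named form, and that form is the two-class one.

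**Other safeguards exist.** A reader might infer that the covariate list is the only protection. The plan also has a historical-control comparison and censoring weights, and it concedes unmeasured confounding. None of these removes confounding by entry score between the two study groups, and that score is measured.

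**Conclusion.** The point holds in a limited form. As named, the primary model and the propensity score control entry severity only between two classes. Any within-class difference in month-0 HAMD-17 is left in both analyses, although the variable is collected, defines the endpoint and is used in continuous form elsewhere in the plan.

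The size rests wholly on assumed slopes and imbalances. With no true effect, the residual OR is about 0.76 to 0.99 in one direction and about 1.06 to 1.22 in the other. Weighted analysis on the same two classes leaves from 0.3 to about 5.5 percentage points. The two classes already remove roughly 60–75% of the confounding by score. What remains is modest against a planned OR of 0.41 to 0.44: it would not create the planned effect, but could shift an estimate by several points either way. The document does not support saying that the primary result will be biased in favour of rTMS. It is worth changing because the remedy is nearly free, and because the sensitivity analysis as listed cannot reveal the problem.

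**What to change.** 1. Add the continuous month-0 HAMD-17 total to the primary logistic model, in place of or beside response/remission.
2. Add the same term to the propensity score, and include it in the standardised-difference balance check after weighting.
3. Settle any further covariates, in dated wording, before anyone involved in the choice sees outcomes by group. The study is open-label, so data fixation alone does not guarantee this.

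The cost is one more model term and a change of wording. Table 1 already schedules the score at month 0 for both groups, so no new data are needed. The article gives the trial status as ongoing.

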#### Secondary and other outcomes

As for the primary outcome, the rates and between-group differences, and adjusted odds ratio (95% CI) will be estimated for the relapse/relapse rate, response rate, and remission rate at 3, 6, and 9 months after enrollment, respectively. Kaplan–Meier curves will be constructed for the duration of the sustained treatment response and sustained remission, and the log-rank test and Cox proportional hazards models will be performed for the between-group comparisons.

The change in the total scores of the HAMD-17, MADRS, QIDS, and PHQ-9 from the baseline (before the introduction of maintenance therapy) will be analyzed using a random-effects model with group, baseline total score, age, sex, time point, and interaction between the time point and the group as explanatory variables and individual as random effect, for all the data at 3, 6, 9, and 12 months.

Frequency distributions of the worst severity of the adverse events and equipment failure will be summarized. Treatment-related adverse events, serious adverse events, and discontinuations owing to adverse events will also be summarized.

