### Participants

#### Inclusion criteria

Participants with MDD above the age of 18 years who responded or remitted to 3–6 weeks of acute rTMS therapy will be included. In Japan, rTMS is indicated for patients who have failed to respond to at least one or more antidepressants; thus, these patients will be included in this study. All the participants must understand and be willing to adhere to the 12-month maintenance therapy schedule. The researchers will obtain informed consent from the participants who meet the criteria.

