#### Power and sample size calculation

In the previous meta-analysis of maintenance rTMS therapy, the response rates at 3 and 6 months in the group with and without maintenance rTMS therapy were 76.2% and 61.1%, and 56.1% and 38.5%, respectively [29]. Applying the Weibull distribution to the 3- and 6-month response rates, the 12-month response rate was estimated to be 40.9% for the maintenance rTMS group and 20.7% for the no maintenance rTMS group, with an estimated difference of 20%. Considering the relapse and recurrence rates, the previous randomized controlled trial of maintenance therapy in patients who responded to pharmacotherapy reported 44.4% in the pharmacotherapy-only group and 24.2% in the rTMS maintenance therapy group, with a 20.2% difference between the groups [30]. Based on these previous studies, we estimated that the relapse/recurrence rate without maintenance rTMS was 45–60%, and the add-on effect of maintenance rTMS was 20%. To detect a 20% additional effect of maintenance therapy, the required sample size varies from 109 to 130 patients for a 45 ~ 60% relapse/recurrence rate in the pharmacotherapy-only group (chi-squared test with two-sided alpha = 0.05 and power = 80%). Since this study plans to conduct a multivariable analysis adjusting for the background factors, the power was set as high as 90%. Assuming that the proportion of participants who drop out without any evaluation of efficacy is 15%, the required number of participants would be 150 in each group.

From the viewpoint of detection of rare adverse events in the maintenance rTMS group, with 150 participants, at least one event with a 2% probability with a 95% chance is expected. Therefore, based on the perspective of comparing the efficacy and collecting safety information, the target number of study participants was set at 150 in each group, with a total of 300 participants.

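### The symptom-score model lets the group effect vary by visit but fixes one baseline-score slope; if self-selected groups differ at entry and that slope changes over time, visit-specific differences are distorted

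*Protocol article*

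**What the plan says.** Under Secondary and other outcomes, the protocol article names the response as "The change in the total scores of the HAMD-17, MADRS, QIDS, and PHQ-9 from the baseline". It fits a "random-effects model with group, baseline total score, age, sex, time point, and interaction between the time point and the group as explanatory variables", with "individual as random effect, for all the data at 3, 6, 9, and 12 months". Baseline score appears once, as a main effect, and time point by group is the only interaction.

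The Primary outcome section leaves room for further covariates to be settled before data fixation. No such clause is attached to the symptom-score model, so its terms read as a stated specification.

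On how the groups arise, Study overview says "the patients will be classified to a group (I) or (II) according to their preferences". Inclusion criteria admit participants who "responded or remitted to 3–6 weeks of acute rTMS therapy will be included". The inverse probability weighting under Sensitivity analysis is stated for the primary outcome only.

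**The concern.** A model that gives each visit its own group effect but only one baseline slope treats the entry score as equally predictive of change at months 3, 6, 9 and 12. If it is not, the adjustment is too strong at some visits and too weak at others. With groups balanced at entry this does little harm, because there is no gap to mis-adjust. Here balance is not expected by design: allocation follows preference, and a remitter (HAMD-17 of 7 or less) and a responder (a fall of at least 50%) can enter at quite different scores. The protocol itself adjusts the primary analysis for response or remission status at enrollment.

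Any mis-adjustment has to go into the group effects that are free by visit. A group difference at month 3 or month 12, or a trend in that difference, could then be partly an artefact of the entry gap.

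**Working it through.** The protocol states no figure for these models, so there is nothing to reproduce. The check is algebra, then simulation under assumptions.

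**Inputs from the protocol article**
- Model terms, visits and random effect: as quoted above.
- Group size: "the required number of participants would be 150 in each group".
- Loss: the assumption that "the proportion of participants who drop out without any evaluation of efficacy is 15" per cent. This leaves 150 × 0.85 = 127.5, so about 127 per group.
- Test level: two-sided 5%.

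**Algebra**

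Let b_t be the true slope of the follow-up score on the entry score at visit t. The slope of change on entry score is b_t − 1, so deviations from the mean slope are the same on either scale. Let D be the entry gap between groups, and suppose there is no treatment effect. The expected group difference in change at visit t is then (b_t − 1) × D. With complete data and a random intercept, the common-slope model removes (mean b − 1) × D at every visit. What remains is

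bias at visit t = (b_t − mean b) × D.

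These residues sum to zero over the four visits, so the visit-averaged effect is not biased. If D = 0 or b_t is constant, every residue is zero.

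**Putting numbers in (assumed; the documents give no score distributions)**

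Suppose b_t falls evenly from month 3 to month 12.
- From 0.8 to 0.5: mean 0.65, so the end visits deviate by ±0.15. Bias is ±0.15 at D = 1, ±0.30 at D = 2 and ±0.45 at D = 3.
- From 0.8 to 0.35: mean 0.575, so the end visits deviate by ±0.225. Bias is ±0.225 at D = 1, ±0.45 at D = 2 and ±0.675 at D = 3.

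**Simulation A.** No true group effect, 127 per group, baseline SD 3.5, residual SD 5, exchangeable correlation 0.6, complete data, 1,500 replicates. Rejection rate of the 3-df time-by-group test at nominal 5%:

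| Entry gap (in SD) | slopes 0.8 to 0.5 | slopes 0.8 to 0.35 |
|---|---|---|
| 1.5 (0.43) | 10.0% | 16.1% |
| 2 (0.57) | 12.3% | 24.8% |
| 3 (0.86) | 28.7% | 51.9% |

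At a 1-point gap with the milder slopes the rate is about 6%. For the 3-point gap with the milder slopes, repeat runs gave about 23% to 29%. Simulated biases at D = 3 with the steeper slopes were +0.68 and −0.67, against ±0.675 from the formula.

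**Single-visit tests.** The SD of each visit estimate is about 0.65.
- A bias of 0.15 is 0.15/0.65 = 0.23 standard errors, which gives about 6% rejection.
- A bias of 0.45 is 0.69 standard errors, which gives about 11%.
- A bias of 0.675 is 1.04 standard errors, which gives about 18%.

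Simulation agrees: about 5% to 11% at months 3 and 12 for gaps of 1 to 2 points, and 10% to 18% for 3 points. Months 6 and 9 stay near 5% to 7%.

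**Simulation B.** Different assumptions: baseline SD 3, between-person SD 3, residual SD 3.5, 5% loss per visit, and slopes on change of −0.40, −0.55, −0.70 and −0.80; 1,000 replicates.

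| Entry gap | bias at months 3 / 6 / 9 / 12 | time-by-group rejection |
|---|---|---|
| 1 | +0.20 / +0.06 / −0.09 / −0.20 | 8% |
| 2 | +0.39 / +0.08 / −0.21 / −0.42 | 16% |
| 3 | +0.58 / +0.13 / −0.34 / −0.60 | 35% |

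With steeper slopes (−0.3 to −0.9), rejection was 12%, 33% and 66%. The visit-averaged effect stayed within 0.07 points of zero throughout. With no gap or a constant slope, rejection was 5% to 6%.

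**With baseline by time point added.** In simulation B every visit-specific bias was within about 0.04 points of zero where the slope varied, and rejection was 4% to 6%. The SD of the month-12 estimate was 0.69 to 0.70 instead of 0.65 to 0.68 at a 3-point gap, and almost unchanged at smaller gaps.

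**The case against.** The strongest reply is that the distortion needs two things the documents do not establish: an entry gap, and a baseline slope that changes across visits. That the slope weakens with time is a general expectation, not a finding of this protocol. Without either condition the stated model is unbiased. It is a common baseline-adjusted repeated-measures model, not one that is wrong on its face. This stands.

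The larger error rates also need large gaps. Three points is 0.86 SD under the assumed baseline SD of 3.5, and restricting entry to responders and remitters limits the spread of scores. For gaps of 1 to 2 points the bias is a fraction of a point, about a quarter to two thirds of a standard error. This stands too.

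A reader might infer that the model exists to show whether benefit grows or fades when sessions go from weekly to biweekly, so that its main purpose is compromised. The documents do not support that. The outcome is listed as change in scores since enrollment, and no section names the time-by-group term as a hypothesis of interest.

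The reply does not remove the point itself. The terms are explicitly listed, the planned weighting does not extend to these models, and preference allocation makes an entry gap a realistic possibility. A fuller analysis plan, not shown, may already carry the extra term; the article's list does not.

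**Conclusion.** The point holds as a conditional weakness in secondary analyses. If the groups differ at entry and the baseline slope changes over visits, the stated model moves part of the entry gap into the month-specific group differences and the time-by-group term. For gaps of 1 to 2 points under the simulation A assumptions, the bias is about 0.15 to 0.45 points at months 3 and 12, with error rates modestly raised for single visits and more clearly for the interaction test. A 3-point gap raises these to about 23% to 52% for the interaction and 10% to 18% for single visits. All these sizes rest on assumed variances, correlation, slopes and gaps.

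A reader might go further and conclude that the overall group effect on symptom scores, or the trial's main result, is biased by this choice. Neither follows. The visit-averaged effect is essentially unbiased, and the primary logistic analysis and its weighted version do not use this model. Nor would the added term deal with unmeasured confounding from preference allocation, which the Discussion already acknowledges as a limitation. The change is an optional improvement.

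**What to change.** In the Secondary and other outcomes section, add the interaction of baseline total score with time point to the models for HAMD-17, MADRS, QIDS and PHQ-9. State that time point is a categorical factor, and take the group differences at months 3, 6, 9 and 12 from that model.

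The cost is three degrees of freedom per model, a very small loss of precision and a change of wording. It needs no new data. The trial is described as ongoing, so the term is best fixed before the outcome data are examined; adding it afterwards would look post hoc.

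### The symptom-score models omit three factors that the plan adjusts for in the primary outcome, leaving these preference-based comparisons open to residual confounding

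*Protocol article*

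**What the plan says.** The Study overview section of the protocol article makes patient preference the basis of group membership: "Random allocation to both the groups will not be performed and the patients will be classified to a group (I) or (II) according to their" (the sentence closes by naming that preference).

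For the primary outcome, the Primary outcome section lists the covariates of the logistic model: "age, sex, number of depressive episodes, duration of current depressive episode, concomitant medication, and status at enrollment (response/remission), and others to be determined" before the data are fixed. The Sensitivity analysis section builds the propensity score from that same list, and gives its scope: "we will analyze the primary outcome with inverse probability of treatment weighting (IPTW) to ensure the comparability" of the groups.

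The Secondary and other outcomes section treats three kinds of secondary outcome differently:

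- Relapse, response and remission rates follow the primary analysis: "As for the primary outcome, the rates and between-group differences, and adjusted odds ratio (95% CI) will be estimated".
- The score-change models for HAMD-17, MADRS, QIDS and PHQ-9 are specified "with group, baseline total score, age, sex, time point, and interaction between the time point and the group as explanatory variables", with the individual as random effect.
- For sustained response and sustained remission, "the log-rank test and Cox proportional hazards models will be performed for the between-group comparisons". No stratification or weighting is given for the log-rank test, and no covariates are given for the Cox models.

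**The concern.** With allocation by preference, any prognostic factor that differs between the groups can pass for a treatment effect unless the analysis accounts for it. The plan accepts this for relapse, and its Discussion says that preference may lead to overestimating the effect of maintenance rTMS.

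Relapse is defined as a HAMD-17 total of 14 or more, so the primary outcome is a cut on the same scale that the main score model analyses. A factor worth adjusting for when the score is cut at 14 has no obvious reason to be dropped when the score is analysed as it stands, and the article gives none.

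The Statistical analysis section applies the same two-sided 0.05 threshold to all reported p-values. A thinly adjusted score difference would then be read on the same footing as the fully adjusted primary result, and could appear to confirm or contradict it for reasons of patient selection.

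**Working it through.** The plan gives no figure on this point to reproduce. The check is a comparison of covariate lists, followed by an illustration on assumed values.

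**Step 1: the lists side by side**

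| Factor | Primary model and propensity score | Score models |
|---|---|---|
| Age | yes | yes |
| Sex | yes | yes |
| Number of depressive episodes | yes | no |
| Duration of current episode | yes | no |
| Concomitant medication | yes | no |
| Response/remission at enrolment | yes | not by name; largely through baseline total score |
| Further factors to be decided before data fixation | yes | no such clause |

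On enrolment status: all entrants have responded or remitted, and remission is a HAMD-17 total of 7 or less. The status variable is therefore essentially a cut of the enrolment HAMD-17 score, which the HAMD-17 model already contains in full. The other three models contain the baseline of their own scale. That leaves three named factors with no counterpart.

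**Step 2: possible size in a score model**

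Inputs from the document: 150 per group and 15% dropout, so 150 × (1 − 0.15) = 127.5, taken as 127 per group.

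Assumed inputs, not in the document:
- SD of HAMD-17 change: 6.
- Partial correlation r of the omitted factors, taken together, with the change: 0.2 to 0.3.
- Group imbalance d remaining after adjustment for baseline score, age and sex: 0.3 to 0.5 SD.

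Bias = r × SD × d:
- low: 0.2 × 6 × 0.3 = 0.36 points
- high: 0.3 × 6 × 0.5 = 0.90 points
- d = 0: no bias

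Standard error of a difference at one visit = 6 × √(2/127) = 0.753.

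Type I error with no true effect = P(|Z + bias/SE| > 1.96):
- low: 0.36/0.753 = 0.478, giving 0.077
- high: 0.90/0.753 = 1.195, giving 0.223
- no imbalance: 0.05

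This uses a single visit and an unadjusted standard error, not the planned repeated-measures model, and it lets the omitted factors act in one net direction.

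**Step 3: the plain log-rank test**

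A simulation took 127 per group, visits every 3 months, 50% control relapse at 12 months (within the plan's 45–60%), no treatment effect, and one omitted binary factor with an assumed hazard ratio of 1.5 to 2.5. The rejection rate at a nominal 5% was:

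| Imbalance in the factor | Type I error |
|---|---|
| none | about 5% |
| 10 percentage points | 6–8% |
| 20 percentage points | 8–17% |
| 30 percentage points | 10–30% |

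This too rests on assumed imbalance and prognostic strength.

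**The case against.** The strongest reply has four parts.

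- Baseline severity, a natural prognostic factor for score change, is already in the score models, and it stands in for enrolment status. This is right, and it reduces the gap from four factors to three.
- An article may leave Cox covariates to the full plan, and a Cox model beside a log-rank test is the usual vehicle for adjustment. This also stands. A reader might infer that the whole time-to-event comparison is unadjusted, but the text leaves the Cox covariates unstated; it does not say there are none. A crude Kaplan–Meier curve with a log-rank test beside a Cox model is ordinary practice.
- Limiting IPTW to the primary outcome, as the plan does ("we will analyze the primary outcome with inverse probability of treatment weighting (IPTW"), is a legitimate choice for a sensitivity analysis. This stands.
- The numerical illustration rests wholly on outside assumptions. This stands as well: it shows what could happen, not what will.

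None of this removes the mismatch in the score models. Their covariates were not left to another document. They are listed in full, and without the open clause that the primary model has. An analysis plan that follows the wording would carry the gap forward.

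**Conclusion.** The point holds for the four score models. They omit number of depressive episodes, duration of the current episode and concomitant medication, all of which the plan adjusts for in the primary outcome. With groups formed by preference, the score comparisons are open to residual confounding by those three factors.

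The size is unknown. Under the assumptions in the working it is about 0.4 to 0.9 HAMD-17 points, with a single-visit type I error of about 8% to 22% in place of 5%. With no residual imbalance there is no bias.

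A reader might go further and infer that these results will be biased, or that the trial's main conclusion is at risk. The document supports neither. It gives no imbalance and no prognostic strength, and omitted factors may offset one another. The primary outcome has its own multivariable adjustment, IPTW, censoring weights and a historical comparison, and the secondary relapse, response and remission rates receive adjusted odds ratios. The matter is confined to secondary outcomes, but it is an avoidable inconsistency that should be corrected.

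**What to change.** - In every score model, add the covariate set of the Primary outcome section, including any factors added before data fixation, and keep the baseline total score. Use enrolment values. This matters most for concomitant medication, which is also recorded throughout follow-up.
- State the same set for the Cox models and base the time-to-event inference on the adjusted Cox estimate. Label the plain log-rank test and the Kaplan–Meier curves as descriptive.
- Extending IPTW to the secondary outcomes is optional.

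The cost is a few lines in the analysis plan. The covariates are already needed for the primary model and the propensity score, so no additional data, patients or software are required, and the sample size does not change.
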